### In summary, what is not known on this topic

Even though over 400 different smoking cessation apps are available, the quality of most of them is poor [13, 16–18], there are few published randomized trials of smartphone apps for smoking cessation, most of these trials were conducted in very small samples, and their results are inconclusive overall [19, 20, 22, 24]. It is not known whether these apps actually help people stop smoking and maintain abstinence over several months, neither is it known whether these apps elicit quit attempts in current smokers or improve NRT usage. Our study will address these important questions, using a sample size much larger than in previous trials, which will provide sufficient statistical power. Our study includes a control group that uses a “placebo” app, which reinforces the likelihood that any observed association will be causal.

The value of the mobile health industry is projected to be 59 billion USD in 2020 [15]. Health apps are massively used, even though very few of them have ben rigorously evaluated, it is therefore important to evaluate these apps in randomized controlled trials.

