## Methods/design

### Objectives

The objective is to test whether the Stop-tabac smartphone application (iOS and Android) improves smoking cessation rates in current smokers and helps them maintain abstinence over 6 months, compared with quit rates observed in a control group, and to measure the size of this effect.

Secondary objectives are:
To study whether the outcome is influenced by the characteristics of participants, such as dependence level, demographics (sex and age), smoking history, and depression.To assess whether the app has any effect on motivation to quit, quit attempts, use of NRT, e-cigarettes and heated tobacco products, number of cigarettes smoked per day, and perceived usefulness of the app.

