#### Outcomes

##### Primary outcome

The primary outcome is smoking cessation: the proportion of participants at the 6-month follow up who report they have not smoked even a puff of tobacco in the previous 4 weeks.

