##### Secondary outcomes

Secondary outcomes are:
Smoking cessation: proportion of participants who report they have not smoked even a puff of tobacco in the previous 7 days, assessed at each follow-up.Smoking cessation as defined in the Russell Standard [36]: proportion of participants at the 6-month follow up who report they smoked ≤5 cigarettes in the past 6 months but did not smoke even a puff of tobacco in the past 7 days, and proportion of participants at the 4-week follow up who report they smoked ≤ 5 cigarettes in the past 4 weeks but did not smoke even a puff of tobacco in the past 7 days.Abstinence from both smoking and vaping: the proportion of participants who report they did not smoke any tobacco or use nicotine-containing e-cigarettes or heated tobacco products after their target quit date, assessed at each follow up.Nicotine use: the proportion of participants who used nicotine therapy, nicotine-containing e-cigarettes or heated tobacco after their target quit date, assessed at each follow up.Perceived usefulness of the app: the question reads: “Did the *Stop-Tabac* app for mobile phones help you quit smoking?”, and is answered on a Likert-type scale with 6 response options ranging from “Yes, enormously” to “On the contrary, it made me smoke or start smoking again”, assessed at each follow up.App use: the proportion of participants who report using any smoking cessation app after their target quit date, assessed at each follow up.

Among those who smoke at follow up:
Intention to quit smoking: the proportion of participants who answer each of the response options to the question: “Do you intend to quit smoking? (response options: I have firmly decided to quit/I consider quitting/No), assessed at each follow up.Quit attempts: the proportion of participants who report they seriously tried to quit smoking after their target quit date (response options: yes/no), assessed at each follow up.Amount smoked: mean number of cigarettes smoked per day, and change since baseline in cigarettes per day (mean change score), assessed at each follow up.

Secondary outcomes from data collected automatically by the app:
Duration of app use (mean number of days between the first and last use of the app) and frequency of app utilization (mean number of times the app was opened), recorded automatically at individual level, assessed at 6-month follow up only.

Inclusion criteria:

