#### Intention to treat, missing data

For the primary outcome, participants will be evaluated in an intention-to-treat analysis, with the baseline number of participants as the denominator. Participants absent at follow-up will be counted as smokers, except those who are dead. We will conduct sensitivity analyses with different assumptions for missing data. For each follow-up questionnaire, non-responders will be counted as smokers for this specific questionnaire. A participant who is missing at the 1-month follow up but then returns as a non-smoker for the 6-month follow up will be counted as smoker for the 1-month follow up only.

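### Quit attempts and cigarettes per day are compared only among follow-up smokers, a group the app itself helps define, so these comparisons do not estimate the effects named in the objectives

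*Protocol article*

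**What the plan says.** The Objectives section states a causal secondary aim: "To assess whether the app has any effect on motivation to quit, quit attempts, use of NRT", and the same list goes on to daily cigarette consumption.

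The Secondary outcomes section then puts three outcomes under the line "Among those who smoke at follow up", each assessed at every follow-up:

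- intention to quit, reported as the share choosing each answer;
- quit attempts, defined as "the proportion of participants who report they seriously tried to quit smoking after their target quit date";
- amount smoked, as a mean per day and a mean change from baseline.

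Other self-reported outcomes in that section, such as nicotine use and app use, carry no such restriction. The variable that defines the subgroup is in essence the reverse of the main endpoint: "The primary outcome is smoking cessation: the proportion of participants at the 6-month follow up" reporting no puff in the previous 4 weeks. The section on intention to treat and missing data gives the baseline denominator for the primary outcome. No version of the three outcomes over all randomized participants is stated.

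**The concern.** Randomization makes the two arms comparable as randomized. It does not make follow-up smokers in one arm comparable with follow-up smokers in the other when the app changes who still smokes.

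For quit attempts the problem is structural. Every participant enters as a daily smoker, so anyone abstinent at follow-up has made an attempt. The smokers-only comparison drops these certain attempters and drops more of them from the arm with the higher quit rate. An app that turns failed attempts into successful ones would look as if it discouraged attempts. The background section says of such apps "neither is it known whether these apps elicit quit attempts in current smokers or improve NRT usage", and the study promises to address that question, so the sign of this comparison matters.

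For cigarettes per day the people removed also differ between arms, but whether they were lighter or heavier smokers is not known in advance.

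**Working it through.** **Inputs from the article (Sample size calculation).** Quit rates at 6 months are 12.5% (app) and 10% (placebo), with 2600 per arm, 80% power and 95% confidence.

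**The plan's own figure.** For two proportions with two-sided alpha 0.05 and 80% power, the usual formula gives 2507 per arm (5014 in total), or 2586 per arm (5172) with continuity correction. At 2600 per arm the power is 81.4%, or 80.2% with the correction. The stated 5200 is reproduced.

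**Size of the smokers-only sets.** App: 2600 × 0.875 = 2275. Placebo: 2600 × 0.90 = 2340. They differ by the very effect the trial seeks.

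**Quit attempts.** Let A be the share of all randomized participants who made a serious attempt and q the quit rate. With every abstainer an attempter, the rate among smokers is (A − q)/(1 − q). The article gives no A, so a range is assumed. The calculation treats smoking at follow-up as the complement of the primary outcome and takes everyone's answers as known. With A equal in both arms, the true difference is 0. The observed difference is −(1 − A) × 0.025/(0.90 × 0.875). A true gain in the app arm shows with the wrong sign if it is below 0.025 × (1 − A)/0.90. The standard error is the square root of p₁(1 − p₁)/2275 + p₀(1 − p₀)/2340.

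| A (assumed) | Placebo smokers | App smokers | Difference, points | Standard error, points | Sign reverses for true gains below |
|---|---|---|---|---|---|
| 30% | 22.2% | 20.0% | −2.2 | 1.2 | 1.9 |
| 50% | 44.4% | 42.9% | −1.6 | 1.5 | 1.4 |
| 60% | 55.6% | 54.3% | −1.3 | 1.5 | 1.1 |
| 80% | 77.8% | 77.1% | −0.6 | 1.2 | 0.6 |
| 90% | 88.9% | 88.6% | −0.3 | 0.9 | 0.3 |

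Differences are taken before rounding. Two examples at A = 60%:

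- a true rise to 61% gives (0.61 − 0.125)/0.875 = 55.4% against 55.6%, shown as −0.1 point;
- a true rise to 62% gives 56.6% against 55.6%, shown as +1.0 point, half its real size.

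**Cigarettes per day.** Assume a mean of 14 in those who smoke under either app, and a mean e in the extra 2.5% who quit only with the full app. The placebo smokers' mean is (0.875 × 14 + 0.025 × e)/0.90, and the app smokers' mean is 14. Over all randomized participants with abstainers at 0, the app minus placebo difference is −0.025 × e.

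| e (assumed) | Smokers-only difference | All-randomized difference |
|---|---|---|
| 7 | +0.19 | −0.18 |
| 10 | +0.11 | −0.25 |
| 14 | 0.00 | −0.35 |
| 18 | −0.11 | −0.45 |

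The smokers-only result goes against the app, is neutral or favours it, depending only on e. Its standard error, for an assumed SD of 6.4 to 8, is that SD × √(1/2340 + 1/2275), or about 0.19 to 0.24.

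**The case against.** **The shift is small against sampling error.** This stands. At A = 60% the 95% interval is about ±2.9 points around a bias of 1.3. A true rise from 60% to 61% would be detected with only about 11% power even over all 2600 per arm.

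**Attempt rates are likely to be high.** Participants must set a quit date within a month and commit to it, so A near 80% or 90% is plausible and the bias is then 0.6 or 0.3 points. This also stands, although the article gives no rate, so the full range has to be shown.

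**Intention to quit belongs to smokers.** Largely right. The item is "Intention to quit smoking: the proportion of participants who answer each of the response options to the question" about intending to quit, which has natural meaning only for people who smoke. A smokers-only table is reasonable as description, but a difference between arms in it is not an effect of the app.

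**Non-responders.** The article says "For each follow-up questionnaire, non-responders will be counted as smokers for this specific questionnaire". A reader might infer that people with no data will fill a large part of the smokers-only denominators. The article does not support that. The paragraph opens with the primary outcome and deals with classifying abstinence, the three items rest on reported answers, and no response rate is given. At most, the denominator is unclear.

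**An all-randomized analysis of cigarettes per day partly repeats the cessation result.** True. In the calculation above the whole difference comes from the extra quitters at zero. It is still a comparison of the groups as randomized.

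**Conclusion.** The mismatch holds: the objective asks for effects of the app, and the stated population is selected by the outcome the app targets. For quit attempts the bias has a known direction, against an effective app, and at the planned quit rates amounts to 0.3 to 2.2 points for A from 90% to 30%. It can reverse the sign of small true gains. It is below one standard error at A of 60% or more, slightly above one at 50%, and approaches two only at 30%.

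Two stronger readings should be resisted. One is that the objective cannot be answered at all; gains above the break-even values keep their sign, and at A = 60% a 2-point gain still shows, at half its size. The other is that the app arm will look worse on cigarettes per day; that holds only if the extra quitters would have been lighter smokers, which the article does not establish.

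The sizes rest on the planned 6-month quit rates and on assumed values for attempts and consumption. The selection itself does not depend on the assumed attempt and consumption values. It arises whenever the app changes who still smokes.

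**What to change.** - Make the between-arm comparison of quit attempts over all randomized participants, with abstainers counted as having attempted.
- Do the same for cigarettes per day, with abstainers at 0.
- State a rule for non-responders on both items. One option consistent with counting missing as smoking is no attempt and baseline consumption, with a responders-only sensitivity analysis.
- Keep the smokers-only results, including intention to quit, as descriptive tables limited to responders, and say that differences in them are not read as effects of the app.

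No new data are needed: smoking status is a required answer in every follow-up questionnaire, and baseline forms are complete. The cost is a change of denominator, two derivation rules and the non-responder rule. The downside is that the all-randomized cigarettes-per-day result partly restates the cessation effect and depends on the non-responder rule, which is why the sensitivity analysis should accompany it.

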#### Informed consent

The online consent form describes the study, risks and benefits, and how confidentiality is maintained, and explains the data collection and data sharing procedures. We will wait until the end of the study to inform participants of the control group procedure and of the placebo version of the app. Participants receive the intervention at no charge and are not paid.

#### Enrollment

Interested participants are directed to the Apple App Store and Google Play Store, where the app will remain available during the whole study and where they can download the app on their smartphone. At this point, the app only displays a screen that instructs participants to visit the study website where they can obtain a personal code that gives them access to the app. Once on the website, participants read an information page about the study, complete a consent form, and indicate their e-mail address. Participants access the baseline screening questionnaire through a link in an e-mail message, which ensures that we have a valid e-mail address for each of them.

#### Randomization

Participants are randomized only after we receive the baseline survey and the consent form, and after we verify eligibility. Eligibility is assessed automatically by computer algorithms. We perform an automated check of e-mail addresses, names, age, and sex, to avoid double registration of participants. Once a candidate is declared eligible, randomization is automatically performed by a computer using a list of random numbers, with a 1:1 ratio and using simple randomization, with no strata or block. After randomization, participants receive a personal code number in an e-mail message, they insert this code number manually in the app on their smartphone, and at this point they can access either the complete Stop-tabac app or to the placebo app. This procedure ensures that participants register only once, that all of them open the app, and that they have access to their intended intervention only. Participants who do not manually enter their personal code in the app do not have access to any version of the app and are excluded after randomization. Access to the app is restricted to study participants during the study; non-participants cannot access or download the app.

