Daily cigarette smokerHas been a daily smoker for at least 1 yearAge ≥ 18 yearsSets a target quit date within 1 month of enrollment, and commits to quit on this dateProvides informed consent onlineCommits to complete all follow-up questionnairesCommits to use the appOwns a smartphone (Android or iOS) and has regular access to e-mailProvides a postal address, a telephone number, and a valid e-mail addressLives in Switzerland or in France

The exclusion criterion is prior use of the Stop-tabac app for smartphones (self-report).

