#### Blinding

Participants are blinded to their assignment group and to the existence of a placebo group. The placebo app is also named Stop-tabac - it looks almost the same as the complete app but with fewer features. Thus, control participants may not easily realize that they receive a placebo app. Participants will be informed about the placebo-controlled study design after the end of the study only, and they will be given access to the full version of the app at this point. It is ethical to avoid informing participants of the placebo procedure, because informing them could jeopardize the blinding and stimulate them to use other smartphone apps, thus contaminating the control group. It is ethical to use a placebo-controlled study design because we do not know whether the Stop-tabac app or any other similar app is effective for smoking cessation.

For baseline and follow-up surveys, online data collection is fully automatic, and thus, there is no bias in online assessments. People who do not respond to the online survey receive the follow-up questionnaires by postal mail, and those who do not respond to the postal communication answer the questionnaire over the phone. Assistants who send text or WhatsApp reminder messages and who collect questionnaires by post and over the phone are blinded to the group assignment of participants, to avoid bias. The data analyst is blinded too. The only person with access to the code linking names and group membership is a computer expert who works under the supervision of the first author ([name]), and the data will be unblinded only after the main analysis is finished. There will be no unblinding during the trial.

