#### Potential bias

Participants consist of volunteers and may not be representative of all smokers. We will compare our sample to representative samples of smokers in Switzerland and France. There are no restrictions to obtaining smoking cessation support outside the study. We ask participants whether they used NRT, e-cigarettes, heated tobacco, or smoking cessation apps during the study, and will use this information in our analysis and interpretation of the results.

There is a risk that participants in the more engaging “complete” app (with push notifications) will be more burdened and delete the app or disable the app notifications, but the current content and frequency of reminders have been considered acceptable by app users over the years.

All answers are given via drop-down menus or radio buttons (except names and addresses), and thus only valid answers are recorded. At baseline, participants are required to answer all questions (an incomplete form cannot be sent) and thus there are no missing data. At follow up, answers to the questions on smoking status (any smoking in the past 7 days, 4 weeks, and 6 months) are required, but participants can send an incomplete form as long as they answer these questions. An assistant will enter the data for questionnaires on paper (collected by post or over the phone) by single data entry.

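### The duplicate-registration check leaves out the telephone number and postal address the trial collects, so it cannot guarantee one registration per person

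*Protocol article*

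**What the plan says.** The Randomization section describes the safeguard: "We perform an automated check of e-mail addresses, names, age, and sex, to avoid double registration of participants". After describing the personal access code it concludes: "This procedure ensures that participants register only once, that all of them open the app, and that they have access to their intended intervention only". It also says that people who never enter their code are excluded after randomization.

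The eligibility list makes a postal address, a telephone number and a valid e-mail address conditions of entry. It excludes prior users of the app on self-report alone. The Enrollment section tests an e-mail address by sending a link to it. On data quality, the Potential bias section says: "All answers are given via drop-down menus or radio buttons (except names and addresses), and thus only valid answers are recorded". Names are therefore typed by the participant.

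On missing outcomes the rule is: "Participants absent at follow-up will be counted as smokers, except those who are dead". On blinding: "Participants are blinded to their assignment group and to the existence of a placebo group". The control app shares the product name, and "it looks almost the same as the complete app but with fewer features".

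**The concern.** The guarantee is stronger than the listed fields allow. Someone with a second working e-mail address and a variant of their name, who denies prior use, could pass. Age and sex alone identify nobody among 5200 participants. The two fields that are harder to vary are the telephone number and postal address, because text, postal and telephone follow-up depend on them. Both are held, yet neither is listed for matching.

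The main analysis is a chi-square test on proportions, which assumes one independent record per person. An undetected duplicate puts the same person into the test twice. Because the second registration is a fresh 1:1 draw, half of such people would land in the other arm and could be exposed to both apps. Under the missing-equals-smoking rule, an abandoned first record also adds a counted smoker to the arm where it sits. Whether this moves the comparison, and which way, depends on who re-registers and whether the first record is answered.

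**Working it through.** **Fields held against fields matched**

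| Field | Collected before randomization | Listed for the duplicate check |
|---|---|---|
| E-mail address | yes | yes |
| Name (typed) | yes | yes |
| Age, sex | yes | yes |
| Telephone number | yes, mandatory | no |
| Postal address | yes, mandatory | no |

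The article does not state the matching rule (any field or all, exact or approximate).

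**The plan's own figures.** The Sample size calculation section gives 10% and 12.5% quitting, 2600 per arm, 80% power and 95% confidence (taken as two-sided 5%). The standard two-proportion formula gives 2507 per arm, or 2586 with continuity correction (5172 in total). Power at 2600 per arm is 81.4%. The stated 5200 is reproduced, and the 2.5-point target is the yardstick below.

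**Model.** Let *d* be the share of an arm that re-registers once and is re-randomized 1:1. *d* is an assumption, because the documents give no duplicate rate. When the first record is unanswered it counts as smoking, and the second record quits at the rate of the arm it lands in. When both records are answered they agree, and the person quits at the app rate if either record is in the app arm.

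*Controls only, first record unanswered, no true effect, quit rate p = 10%.*
- App arm: *p*
- Control arm: *p*(1 − *d*/2)/(1 + *d*/2)
- Difference: *p·d*/(1 + *d*/2)

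For *d* = 5%, 130 controls re-register and 65 of the new records fall in each arm. Control: (260 − 13 + 6.5)/2665 = 253.5/2665 = 9.51%. App: 266.5/2665 = 10.00%. Difference: 0.49 points.

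*Equal re-registration, first record unanswered.* Both arms' rates are divided by (1 + *d*). The null difference stays at 0, and a true 2.5 points becomes 2.5/(1 + *d*). At *d* = 5% this is 2.5/1.05 = 2.38.

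Difference, app minus control, in percentage points:

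| Scenario | d = 1% | 2% | 5% | 10% |
|---|---|---|---|---|
| No effect; controls only; first record unanswered | +0.10 | +0.20 | +0.49 | +0.95 |
| No effect; app arm only; first record unanswered | −0.10 | −0.20 | −0.49 | −0.95 |
| No effect; equal in both arms; first record unanswered | 0 | 0 | 0 | 0 |
| No effect; both records answered, any pattern | 0 | 0 | 0 | 0 |
| True 2.5; equal in both arms; first record unanswered | 2.48 | 2.45 | 2.38 | 2.27 |
| True 2.5; controls only; both records answered | 2.49 | 2.48 | 2.44 | 2.38 |

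In the first two rows the approximate two-sided rejection rate rises from 5% to 5.2%, 5.7%, 9.2% and 22.4%. These rates treat every record as independent.

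**The case against.** A reader might infer that duplicates, combined with counting missing as smoking, favour the app. The argument would be that control users hold the reduced app and so have more reason to try again. The documents do not establish this, for four reasons.

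- **Motive.** Participants do not know that a placebo arm exists, so they have no stated reason to expect a different version from a new code. They are not paid, and the control app keeps features that users like. A re-registrant must also deny prior use of an app that carries the same name in both arms.
- **Unanswered first record.** Non-responders are pursued by e-mail, text, post and telephone. If the duplicate gives the same telephone number and address, those routes reach the same person for both records. With both answered, the null bias is zero.
- **Lost codes.** A person who never received a code never enters one, and the Randomization section excludes such people. On that text the first record does not become a counted smoker, and the loss occurs before either app is seen.
- **Inputs.** A *d* of 5% in controls only means 130 people passing the check and denying prior use, with none in the app arm. Nothing in the documents supports that figure, or a higher quit rate among re-registrants.

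It is also fair to say that the matching rule is not shown, so approximate matching might catch name variants, and that an article condenses such detail.

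All of this stands against a claim of direction or size. It does not rescue the guarantee. The prior-use barrier is self-report, and the fields the article chooses to list omit the two that would be most useful. Nor is a control-arm excess impossible: the Control group procedures section itself worries that a placebo app that is too basic would send controls to other support more often.

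**Conclusion.** The point holds as a limit on what the check can deliver. As described, it cannot guarantee that each person registers once and reaches only the intended app. Undetected duplicates break the one-person-one-record basis of the main test and may expose some people to both apps.

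Bias can run either way. It runs towards the app only if controls re-register more often and leave the first record unanswered: about 0.1 to 0.5 points for an assumed 1% to 5% of controls, where 0.49/2.5 is about 20% of the target effect at the upper end. It runs against the app if the app arm re-registers more and leaves the first record unanswered, and towards the null if re-registration is equal and the app works. No duplicate rate is given, so none of these figures is an estimate for this trial. Severity is minor; this is a cheap improvement.

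**What to change.** The Trial status section says recruitment is complete, so the remedy is a data check. The Blinding section places unblinding after the main analysis, so the check should come before that analysis.

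1. Search for duplicates blind to arm, on normalized telephone number and on normalized postal address with age and sex, in addition to e-mail and name. Use an extract without group membership, and review household matches by hand.
2. Keep each person once, in the arm first randomized, and attach answers given under later records. Fix beforehand which answer counts if they conflict and which target quit date applies, since follow-up dates are tied to it.
3. State how a first record whose code was never entered is handled, given both the exclusion in the Randomization section and the baseline denominator in the intention-to-treat section.
4. Report the number of duplicates by first arm, and put that count in place of the word *ensures*.

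The cost is a few hours of data management on data already held, some manual review of people who share a household, and possibly a slightly smaller number randomized. If the count is near zero, the protocol's claim gains the evidence it now lacks.
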